### Efficacy evaluation

#### Objectives

The intervention was designed to reduce victimization and perpetration of physical, sexual, and psychological violence in dating (primary outcomes) and to boost the quality of the romantic relationship as well as conflict management skills and help seeking (secondary outcomes).

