#### Follow-up

At three months after the end of the intervention, the experimental and control group participants will again respond to measurements of conflict resolution skills, victimization and perpetration of violence, and relationship quality. Additionally, they will also fill out the Seeking Help Questionnaire. This instrument, developed by the authors, is composed of three closed questions that inquire whether the respondents sought any sort of help to deal with their affective relationship since they first entered the research website, whom they asked for help, and what the perceived efficacy of the help received was.

Additionally, the Dating SOS participants will be asked to evaluate the impact of the intervention by responding to the Dating SOS Impact Questionnaire, composed of one closed question (How would you evaluate the effects of Dating SOS in your life?) with a multiple choice answer (e.g.: It helped me to end the violent relationship) and three open questions (If Dating SOS made no difference in your life, what do you attribute this to?; If Dating SOS had some effect in your life, what do you attribute this to?; Comment freely about what you thought of Dating SOS).

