### Statistical analysis

Descriptive statistics will be used to describe the characteristics of the participants in the baseline and usability data. The principal analyses will consist of intra- and intergroup comparisons between the baseline and the three-month follow-up on the outcomes of victimization and perpetration of physical, psychological, and sexual violence; quality of the romantic relationship; and conflict management skills. Multivariate analysis of covariance will be used to examine the efficacy of the intervention on these outcomes. The attachment style and the relationship’s violence status will be used as covariates. In addition to this, intergroup comparisons will be conducted using the *t*-test on the three-month follow-up outcome of seeking help. Moderation analysis will be employed to evaluate the differential effects of the intervention based on gender, age, and sexual orientation. A significance level of 0.05 will be adopted.

Omitted or incomplete data will be handled via multiple imputation using the Missing Value Analysis procedure of SPSS Statistics. Intention-to-treat analyses will be carried out, and all randomized participants will be posteriorly included regardless of having completed the intervention or not. The effects of Dating SOS will be estimated utilizing Cohen’s d (where values around 0.2 = small effect size; around 0.5 = medium effect size; and around 0.8 = large effect size).

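### The planned t-test and Cohen's d do not fit the help-seeking questionnaire, and the plan does not say which of its three questions is the endpoint (minor)

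*Protocol article*

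**What the plan says.** The Objectives section lists "conflict management skills and help seeking (secondary outcomes") after the primary violence outcomes.

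The instrument is described under Follow-up, where it is added to the repeated measures: "Additionally, they will also fill out the Seeking Help Questionnaire". It "is composed of three closed questions that inquire whether the respondents sought any sort of help to deal with their affective relationship", and it also asks "whom they asked for help, and what the perceived efficacy of the help received was". No total, count or scale score is described.

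The Statistical analysis section then fixes four things that bear on this outcome:

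- The arms are compared by a t-test, given as a "test on the three-month follow-up outcome of seeking help". No covariates are named for it. The multivariate analysis of covariance for the other outcomes does have covariates: attachment style and the violence status of the relationship.
- "The effects of Dating SOS will be estimated utilizing" Cohen's d, read against the usual small, medium and large benchmarks. No other effect measure is named.
- Under intention to treat, "all randomized participants will be posteriorly included regardless of having completed the intervention or not".
- "Omitted or incomplete data will be handled via multiple imputation using the Missing Value Analysis procedure of SPSS Statistics". No exception is made for a question that does not apply to a participant.

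**The concern.** A t-test compares means, and Cohen's d expresses a difference in means in standard deviations. As worded, the three questions give a yes/no answer, a choice of sources, and a rating that exists only for someone who received help. The plan does not say which of these is the outcome of seeking help, and the consequence differs by question.

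- **Yes/no question.** The test works, but d hides the quantity a reader wants, namely how many more people per hundred sought help. The comparison also forgoes a covariate that is already collected and is likely to be related to the need for help.
- **Perceived efficacy.** This is the only question that looks like a rating, so it is the one to which a t-test and d would most naturally be applied. The comparison would be restricted to people who sought help after randomisation. The Background expects Dating SOS to build skills for seeking help, and Session 4 in Table 1 works on this directly, so the arms would differ in who contributes a rating. Read literally, the all-randomised and imputation rules would also create ratings for help that was never sought.

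At stake is the interpretability of one secondary outcome. The primary outcomes and the sample size are not affected.

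**Working it through.** **Inputs.** From Calculation of the sample size: 610 per arm and 50% dropout, so 610 × (1 − 0.50) = 305 per arm with follow-up data. From Statistical analysis: alpha 0.05, taken as two-sided. The article gives no help-seeking rate, so the rates below are assumptions. It also states no figure for help-seeking that could be reproduced; the 610 was derived for violence prevalence, and nothing here depends on how.

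**1. Is the t-test's p-value wrong for the yes/no question?** On 0/1 data with N participants in total, the pooled t statistic and the Pearson chi-square satisfy t² = (N − 2)χ² / (N − χ²). With N = 610 (305 per arm), the 5% chi-square boundary of 3.841 maps to t² = 608 × 3.841 / 606.16 = 3.853. The t-test's own boundary is 1.9639² = 3.857. The two tests are practically the same.

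Exact enumeration agrees. At 305 per arm, type I error is 0.047 to 0.051 for true rates of 2% to 50%, identical to four decimals for both tests. At 610 per arm the two differ by at most 0.0004. For 20% against 30% at 305 per arm, power is 0.82 by either test.

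**2. What does Cohen's d convey?** For proportions, d = (p2 − p1) / √{[p1(1 − p1) + p2(1 − p2)] / 2}.

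| Assumed rates | Difference | Pooled SD | d |
|---|---|---|---|
| 5% vs 10% | 5 points | √0.06875 = 0.262 | 0.19 |
| 10% vs 20% | 10 points | √0.125 = 0.354 | 0.28 |
| 20% vs 30% | 10 points | √0.185 = 0.430 | 0.23 |

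The same 10-point gain gives two values of d. A doubling of help-seeking (5% to 10%) scores below a rise of one half (20% to 30%). All three lie near the article's small benchmark of 0.2.

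The risk difference for 20% vs 30% would read as 10 points with a 95% CI half-width of 1.96 × √[(0.16 + 0.21)/305] = 1.96 × 0.0348 = 6.8 points, so about 3 to 17 points.

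**3. What does leaving out violence status cost?** Randomisation balances baseline violence in expectation, so the unadjusted comparison is unbiased. Adjustment can only narrow the interval. By how much depends on how strongly baseline violence predicts help-seeking, which the article does not give.

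**4. What if the test were used on perceived efficacy?** Suppose the intervention has no effect on the rating, and the propensity to seek help correlates 0.3 to 0.5 with the rating (assumed). Simulation with 305 per arm, testing seekers only, gives:

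| Assumed seeking rates | Rated per arm | Spurious difference (SD) | False-positive rate |
|---|---|---|---|
| 20% vs 30% | 61 vs 91.5 | 0.07 to 0.12 | 7.5% to 13% |
| 10% vs 20% | 30.5 vs 61 | 0.11 to 0.18 | 8% to 15% |
| 20% vs 40% | 61 vs 122 | 0.13 to 0.22 | 14% to 33% |

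These figures apply only if that test is run, and only under the assumed rates and correlations.

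**The case against.** The article speaks of one outcome of seeking help, in the singular, and the natural reading is the first question. On that reading the p-value is fine, and the difference in means of a 0/1 variable is itself the risk difference. Response formats are not given, so the absence of a usable score is an inference. In the tailoring questionnaire (Step 3) the comparable help-source item allows several answers; a similar follow-up item would give everyone a count of sources, with zero for non-seekers. Scoring may also sit in a fuller protocol or analysis plan.

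Much of this stands, and it limits the point. Four stronger readings might be inferred but are not supported:

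- *That the t-test gives an invalid p-value.* Step 1 of the working shows it does not for the yes/no question.
- *That a biased comparison of perceived efficacy is planned.* No section says that source or perceived efficacy will be tested between arms.
- *That lack of adjustment biases the result or hides a benefit.* If the intervention lowers violence and so lowers the need for help, that happens after randomisation. Baseline adjustment does not remove it.
- *That the outcome is underpowered.* With an assumed 10% to 20% seeking help, about 31 to 61 of 305 per arm would have a rating, and the detectable d would be (1.96 + 0.842) × √(2/31) = 0.71 down to (1.96 + 0.842) × √(2/61) = 0.51. That is the power of a test the article does not plan.

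The objection does not remove the remaining gap. The article itself names the test, the effect measure and the instrument, and these do not match. A count of sources is nowhere described.

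**Conclusion.** The point holds in a limited form and is minor. The plan fixes a test of means and Cohen's d for an outcome described only as three closed questions, without saying which question counts.

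If the yes/no question is meant, the inference is sound, the effect measure is poor, and some precision is given up by ignoring violence status; the amount cannot be computed from the article. If perceived efficacy were tested, the comparison would lose the protection of randomisation and could include imputed ratings of help never sought. That second consequence is conditional, because the article does not state such a test.

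The conclusion rests on the response formats being what the wording of the questions suggests. The seeking rates and correlations in the working are assumptions and only illustrate size.

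**What to change.** In the Statistical analysis section:

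1. Name the endpoint as having sought any help (yes/no) by the three-month follow-up, in all randomised participants. Multiple imputation of this answer for people lost to follow-up can remain.
2. Replace the t-test and Cohen's d for this outcome with the risk difference and its 95% CI. Obtain it by standardisation (marginal effects) from a logistic model adjusted for baseline violence status; the model's own coefficient is an odds ratio, so this step has to be stated.
3. Optionally, give the same estimate among participants with violence at baseline. That group is defined before randomisation, so the comparison within it stays randomised.
4. Describe source of help and perceived efficacy among seekers by arm, without a test, and state that these two questions are not imputed for non-seekers.

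The cost is a few sentences. All the data are already collected, and the sample size does not change. The downside is that there is no between-arm test of perceived efficacy.

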### Ethical aspects

This study was approved by the Committee for Ethics in the Human and Social Sciences of the University of Brasília (approval CAAE 71749317.9.0000.5540).

## Discussion

We believe the principal merit of the present study resides in the development of an innovative strategy based on the qualified use of the internet for education surrounding romantic relationships and the prevention of dating violence among adolescent and young Brazilians, a hitherto unaddressed need in the field. It is hoped that studies based on Dating SOS and the intervention itself will serve, to one extent or another, to strengthen professional practices in prevention and psychotherapy as applied to dating violence, supported by a more nuanced understanding of the phenomenon.

The primary limitation of this study lays in data collection in the pre-testing stage from youths from Brasília, who could be distant in culture and sociodemographic characteristics from their counterparts in other regions of Brazil. Given the vastness of the country and its cultural diversity, it is possible this would result in a loss of cultural sensitivity for the intervention when implemented with youths in small cities, rural areas, and traditional communities, such as indigenous ones. It is also possible that the omission of an evaluation of partner mutability, that is, how influenceable the partner is or is not by the efforts of the intervention user constitutes an important limitation. This could be a target of future studies.

Should there be positive evidence for the intervention’s usability and efficacy, it will become a useful tool for bringing scientific knowledge to adolescents and will contribute to the debate around the broadening of educational services and early interventions that integrate the scope of public policies directed at dealing with violence against women and the promotion of mental health in adolescents of both genders in Brazil. Should the evidence be insufficient or negative regarding the intervention’s efficacy, new studies should correct problems, remedy gaps, and undertake additional testing.

In conclusion, dating violence has an elevated prevalence among Brazilian adolescents. School-based preventive programs have been implemented, but remain isolated initiatives with insufficient reach. Health communication strategies based on scalable technologies are compelling. Taking this into account, we developed Dating SOS, an innovative computer tailored intervention designed to prevent dating violence and improve the quality of affective-sexual relationship among Brazilian adolescents. Its production was based on clear theoretical basis and empirical evidences derived from Brazilian context. The romantic partner changeability and a broader geographic diversity sample should be considered in the design of similar technologies. The usability and efficacy of Dating SOS should be examined in future studies.

## Data Availability

Data are available from the corresponding author on reasonable request.

## Abbreviations

CTI: Computer-tailored intervention
I-Change Model: Integrated change model
UX: User experience
ECR-short: Experience in Close Relationships Scale, short version
CRBQ: Conflict Resolution Behavior Questionnaire
CADRI: Conflict in Adolescent Dating Relationship Inventory
